## Abstract

**Background:**

Postoperative delirium (POD) is an acute disorder of attention and cognition, frequently observed as a complication in elderly individuals undergoing major surgery. Patients undergoing laparoscopic radical prostatectomy (LRP) are particularly vulnerable due to advanced age and comorbidities. Electroacupuncture (EA), as a non-pharmacological intervention, may attenuate neuroinflammation and cerebral injury, potentially reducing the risk of POD. This study aims to evaluate the efficacy of EA in reducing the incidence of POD among elderly patients undergoing LRP.

**Methods:**

This is a double-center, prospective, randomized, patient- and assessor-blinded, sham-controlled trial. A total of 212 eligible participants will be enrolled and allocated in a 1:1 ratio to either the EA group or the sham EA (SEA) group. Participants in the EA group will receive intervention at the acupoints Zusanli (ST36) and Baihui (GV20), initiated 30 min prior to anesthesia induction and maintained for 25–30 min. The primary outcome is the incidence of POD assessed using the 3D-CAM during the first three postoperative days. Secondary endpoints include the duration and severity of delirium, delirium subtypes, pain scores, opioid consumption, catheter-related bladder discomfort, adverse events, and plasma levels of neuroinflammatory biomarkers.

**Discussion:**

Currently, evidence regarding the efficacy of EA in preventing POD specifically in elderly patients undergoing LRP is limited. This randomized controlled trial is designed to address this research gap. If the hypothesis is confirmed, this study will provide evidence for a safe, non-pharmacological strategy to improve postoperative cognitive outcomes in this population.

**Clinical trial registration:**

https://www.chictr.org.cn/showproj.html?proj=240562, Identifier: ChiCTR2500097337.

## Introduction

Delirium is characterized by an acute confusional state marked by abrupt onset of confusion, fluctuating course, inattention, and often altered consciousness (1). POD is a common and serious surgical complication among older patients after surgery (2). A growing body of evidence indicates the strong association between delirium and adverse patient outcomes, including prolonged hospitalization, increased complications, long-term cognitive dysfunction post-surgery, and heightened mortality risk (3, 4). These findings suggest that the prevention and management of POD warrant clinical attention.

Prostate cancer is the second most common cancer and the fifth-leading cause of death from cancer among men (5). Most prostate cancer patients are elderly, who often have more comorbidities and a higher incidence of POD. Previous studies have reported that the incidence of POD in patients undergoing radical prostatectomy ranges from 15.4% to 39.3% (6–8). The United States Cancer Statistics for 2020 revealed that the median age stood at 66 years for prostate cancer (9, 10). As the gold standard for treatment of prostate cancer, in LRP, patients are typically positioned in the Trendelenburg position and require sustained pneumoperitoneum, both of which can increase the risk of POD. Meanwhile, the complexity of cancer radical surgery and the potential postoperative pain may still trigger an inflammatory response, thereby impacting cognitive function (11, 12).

Currently, it is believed that multi-component non-pharmacological interventions (such as the ABCDEF bundle care, pain management, early mobilization, and adequate fluid supplementation) are the most effective methods for reducing POD (13–15). Regarding pharmacological interventions, recent meta-analyses indicate that α_2_-adrenoceptor agonists (specifically dexmedetomidine) are among the most effective strategies for preventing POD. In contrast, evidence supporting the prophylactic use of other agents, such as benzodiazepines, remains insufficient (16, 17). EA, a treatment method that combines traditional acupuncture with modern electrical stimulation techniques, has shown potential in the treatment of cognitive dysfunction in recent years (18, 19). A recent umbrella review also noted that acupuncture was associated with a reduction in postoperative neurocognitive complication (20). However, the mechanism of EA in preventing POD is not yet clear. According to recent studies, EA can inhibit the expression levels of pro-inflammatory cytokines, including IL-1*α*, IL-6, and TNF-α, to counteract neuroinflammation and oxidative stress and alleviate cognitive impairment (21). Phosphorylated tau protein 217 (P-tau 217), a key biomarker closely associated with the pathological mechanisms of neurodegenerative diseases such as Alzheimer’s disease (AD), may also be related to POD. Yet, the correlation between plasma P-tau 217 levels and POD following EA treatment has not been verified and warrants further investigation (22).

As a non-pharmacological intervention, the effectiveness of EA in reducing the incidence of POD has been demonstrated in previous studies, though most of the research has focused on cardiac and lower limb joint surgeries (23, 24). Currently, studies targeting elderly patients with prostate cancer remain limited. Therefore, there is an urgent need for randomized controlled trial to evaluate the efficacy of EA in treating POD following LRP. We hypothesize that EA may mitigate POD in this cohort. Specifically, the acupoints Zusanli (ST36) and Baihui (GV20) were selected for this protocol based on their purported roles in regulating inflammatory responses and improving cerebral function (25), respectively. To test this hypothesis, we designed a double-center, randomized, sham-controlled trial. This study aims to evaluate the efficacy of EA in preventing POD in elderly patients undergoing LRP, employing a methodological framework to minimize bias.

## Methods and analysis

### Trial setting

This study is a two-center, randomized, sham-controlled trial with two parallel arms. The study protocol has been designed in accordance with the Standard Protocol Items: Recommendations for Interventional Trials (SPIRIT) 2013 statement (26). Eligible patients will be enrolled and randomly assigned in a 1:1 ratio to receive either EA or SEA. The trial is currently being conducted at the Affiliated Hospital of Jiaxing University and the Jiaxing Hospital of Traditional Chinese Medicine. Ethical approval was granted by the Ethics Committee of The Affiliated Hospital of Jiaxing University on July 30, 2024 (Approval No. 2024-KY-603) and by the Ethics Committee of the Jiaxing Hospital of Traditional Chinese Medicine on October 28, 2024 (Approval No. S1-2024-0096). The protocol is registered with the Chinese Clinical Trial Registry (Registration number: ChiCTR2500097337). A flowchart illustrating the study procedures is provided in Figure 1. Both groups will receive a standardized perioperative pain relief protocol to minimize confounding factors. Participant enrollment commenced in March 2025 and is anticipated to continue until July 2026. Written informed consent will be obtained from each participant prior to enrollment. The schedule of enrollment, interventions, and assessments is detailed in Table 1.

**Figure 1 fig1:**
[figure not shown]
Flow chart of the study procedure. The diagram outlines the study design and participant timeline, encompassing enrollment, screening for eligibility, baseline assessment, and randomization. A total of 212 eligible elderly patients undergoing laparoscopic radical prostatectomy (LRP) will be randomly allocated in a 1:1 ratio to either the electroacupuncture (EA) group (*n* = 106) or the sham electroacupuncture (SEA) group (*n* = 106). The chart details the intervention phase, postoperative follow-up, assessment of primary and secondary outcomes (including incidence of POD, biomarkers, and adverse events), and final data collection. POD: Postoperative delirium.

**Table 1. tab1:** Data collection methods and clinical assessment time points.

contents	Study period							
	T0	T1	T2	T3	T4	T5	T6	T7
ENROLLMENT								
Eligibility screening	X							
Informed consent	X							
Demographic characteristics		X						
Baseline measures		X	X					
Randomization	X							
INTERVENTION								
EA			X					
SEA			X					
ASSESSMENTS								
Incidence of POD				X	X	X	X	
Onset time of POD				X	X	X	X	
Duration of POD				X	X	X	X	
Severity of POD				X	X	X	X	
Subtypes of POD				X	X	X	X	
VAS scale				X	X	X	X	
Incidence of CRBD				X				
Opioid consumption						X	X	
Blood test indexes					X	X	X	
Perioperative anxiety score	X				X	X	X	
Safety outcomes	Throughout the study period until discharge							

T0:1 day of pre-surgery T1: 30 min before anesthesia T2: during operation T3:6h post-operation T4:1d post-operation T5: 2d post-operation T6:3d post-operation T7: hospital discharge

### Eligibility criteria

The inclusion and exclusion criteria for participants in this study are as follows:

Inclusion criteria

1) Male patients scheduled for elective LRP;2) Participants were 65 years of age or older;3) Participants with ASA classification I to III were included;4) Participants are willing to provide written informed consent;

Exclusion criteria

1) Planned use of epidural or spinal anesthesia (i.e., non-general anesthesia);2) Skin infection, open wounds, or severe dermatological conditions at the selected acupoints (ST36, GV20);3) Pre-existing cognitive impairment, defined as a Mini-Mental State Examination (MMSE) score < 24;4) Pre-existing diagnosis of dementia or other severe psychiatric disorders (e.g., schizophrenia) that may confound delirium assessment;5) History of structural brain lesions with residual neurological deficits (e.g., traumatic brain injury, stroke within the past 3 months, intracranial tumors);6) Presence of an implanted cardiac pacemaker or other implantable electronic devices (contraindication for EA);7) Severe visual, auditory, or language impairments preventing effective communication and assessment;8) Current history of alcohol abuse or drug dependence (to exclude withdrawal symptoms mimicking delirium);9) Concurrent participation in another clinical trial.

### Randomization and blinding

Randomization will be performed by an independent statistician using SPSS software version 26.0, generating a random number sequence to assign participants in a 1:1 ratio to either the EA or SEA group. To ensure a balanced distribution between the two study sites, randomization will be stratified by center utilizing a block randomization method with varying block sizes of 4 or 6. The allocation sequence will be concealed in sequentially numbered, opaque, sealed envelopes, which will be kept in a secure location and opened by the acupuncturist only after the participant has provided informed consent and completed baseline assessments. Given the nature of the intervention, the acupuncturist cannot be blinded to group allocation; however, to minimize bias, this study employs a patient- and assessor-blinded design. Participants will remain blinded to their treatment assignment through the use of a sham procedure with identical device settings (lights and sound), while outcome assessors—including anesthesiologists responsible for intraoperative management and research registrars conducting postoperative delirium assessments—will be strictly blinded to group allocation. Additionally, the statistician performing the final analysis will handle data with coded identifiers to maintain blinding until the analysis is complete, with emergency unblinding permissible only if essential for clinical management of a severe adverse event.

To evaluate the integrity of the blinding procedures, a standardized blinding assessment questionnaire will be administered to all participants immediately following the completion of the intervention. Participants will be required to quantify the intensity of the stimulation sensation—encompassing specific De qi characteristics such as soreness, numbness, distension, or heaviness—and report their perception regarding the nature of the treatment received. The specific details this assessment are presented in Table 2.

**Table 2 tab2:** Questionnaire for the assessment of blinding effectiveness and acupuncture sensation.

Blind Method Assessment Questionnaire
Name:________ Random Number:_________ Date:___________ **Please answer the following questions according to the latest acupuncture experience.**
1. How’s your feel about needle sensation (sensation induced by acupuncture, like sourness, numbness, distending, heaviness, etc) Please ring a number between 0 (no needle sensation) and 10 (unbearable needle sensation)  0 1 2 3 4 5 6 7 8 9 10
2. Do you have acupuncture experience? (Yes No)
3. Do you have electroacupuncture experience? (Yes No)
4. Are you sure you are receiving acupuncture treatment (Yes No)

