**Figure 2 fig2:**
[figure not shown]
Anatomical location of acupoints for the Electroacupuncture (EA) and Sham Electroacupuncture (SEA) groups. The left panel illustrates the location of Zusanli (ST36) on the lower leg and its corresponding sham point. The right panel illustrates the location of Baihui (GV20) on the head and its corresponding sham point. Red dots indicate the true acupoints used in the EA group, while blue dots indicate the non-acupoints used in the SEA group (located approximately 20 mm lateral to the true acupoints).

Participants in the SEA group will receive a sham intervention. Needles will be inserted 20 mm lateral to ST36 and GV20 to a superficial depth of 3–4 mm without manipulation or elicitation of De qi. Although electrodes will be connected and the stimulator light activated to mimic the active group, no electrical current will be delivered. To ensure blinding integrity, patients in both groups will be informed that they may or may not feel the electrical stimulation.

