A comprehensive assessment of efficacy will be conducted by analyzing a series of secondary outcomes. For longitudinal continuous outcomes—such as the HADS-A scores measured at multiple time points—a linear mixed-effects model (LMM) will be used to account for within-subject correlation. For pre-to-post changes in biomarkers (P-tau 217 and S100β), an analysis of covariance (ANCOVA) model will be used, with the baseline value included as a continuous covariate to improve statistical precision. For all other secondary outcomes, continuous variables will be compared using the independent samples t-test or the Mann–Whitney U test; ordinal outcomes (such as CRBD severity) will be analyzed with the Mann–Whitney U test, and binary outcomes will be compared using the *χ*^2^ test or Fisher’s exact test. Safety outcomes, including the incidence of adverse events (e.g., acupuncture-related hematoma, dizziness) and general postoperative complications, will also be compared between the groups using the *χ*^2^ test or Fisher’s exact test. Additionally, to assess the success of blinding, the agreement between participants guessed and actual treatment allocation will be quantified using Cohen’s Kappa coefficient.

Two exploratory analyses will be conducted. First, to identify potential predictors of POD, we will perform separate univariable logistic regression analyses for key intraoperative variables (e.g., duration of anesthesia, estimated blood loss), reporting unadjusted odds ratios and 95% CIs. Second, we will investigate the association between these variables and the treatment effect to generate hypotheses for future research.

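### Question 4 of the blinding questionnaire does not elicit the allocation guess that the planned kappa needs

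*Protocol article*

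**What the plan says.** - **Protocol article, Statistical analysis.** To assess whether blinding succeeded, "the agreement between participants guessed and actual treatment allocation will be quantified", with Cohen's kappa as the measure. No threshold for success is given, and no rule for coding questionnaire answers as guesses.
- **Protocol article, Randomization and blinding.** Every participant completes a questionnaire once, straight after the intervention. They rate the sensation and "report their perception regarding the nature of the treatment received". The section refers to Table 2 for the details.
- **Protocol article, Table 2.** The form has four items. Question 1 is a sensation rating: "Please ring a number between 0 (no needle sensation) and 10 (unbearable needle sensation". Questions 2 and 3 ask whether the patient has had acupuncture, and then electroacupuncture, in the past. Question 4 is the only one about the treatment just given: "Are you sure you are receiving acupuncture treatment (Yes No".
- **Protocol article, Intervention.** EA patients have needles at ST36 and GV20, manipulated to elicit De qi, with 2 Hz stimulation. For the sham arm, "Needles will be inserted 20 mm lateral to ST36 and GV20 to a superficial depth of 3–4 mm". The sham needles are not manipulated and carry no current, but the electrodes are attached and the stimulator light is on. Both groups are told the same thing about possibly feeling the stimulation.

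**The concern.** The analysis section needs each patient's guess of allocation, and the form that is meant to collect it has no item offering EA and sham as answers. Question 4 is the only candidate, and it differs from a guess in three ways:

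- It asks about acupuncture, whereas the randomized contrast is electroacupuncture against sham electroacupuncture. A sham patient has been needled and can truthfully say Yes.
- It asks about certainty. A patient with no opinion and a patient convinced of having had sham would both answer No.
- The protocol does not say that Yes counts as a guess of EA and No as a guess of sham.

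Patient blinding is a headline feature of the design, and the two procedures feel different: one involves deep needling, manipulation and current, the other none of these. Several secondary outcomes depend on the patient's own report (VAS pain, CRBD, HADS-A). If the blinding statistic cannot be interpreted, readers cannot tell whether expectation could have influenced those outcomes.

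**Working it through.** The protocol gives no kappa value, target or expected response rate, so there is no figure to reproduce. The check asks what a kappa from question 4 would measure.

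**Inputs from the protocol.** Allocation is 1:1, with 106 per arm (Trial setting; Figure 1 legend). Question 4 has two answers (Table 2). Needles are inserted in both arms (Intervention).

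**Assumed coding, not in the protocol.** Yes = guess of EA; No = guess of sham.

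**Step 1: what kappa becomes.** Let a = P(Yes | EA) and b = P(Yes | SEA). With equal arms:

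- observed agreement: po = (a + 1 − b)/2
- overall Yes rate: (a + b)/2
- chance agreement: pe = 0.5 × (a + b)/2 + 0.5 × [1 − (a + b)/2] = 0.5
- kappa = (po − pe)/(1 − pe) = [(a + 1 − b)/2 − 0.5]/0.5 = a − b

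So kappa from question 4 is the difference in Yes rates between the arms.

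**Step 2: its value when blinding has failed completely.** Suppose every patient knows the arm. A true guess would then give kappa = 1.0. Let f be the share of SEA patients who nevertheless answer Yes because needles were inserted. Let u be the share of EA patients who answer No because they are not sure. Then a = 1 − u, b = f, and kappa = 1 − u − f.

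| f (SEA answering Yes) | u (EA answering No) | kappa from question 4 |
|---|---|---|
| 0 | 0 | 1.00 |
| 0.50 | 0 | 0.50 |
| 0.50 | 0.20 | 0.30 |
| 0.75 | 0.20 | 0.05 |
| 0.90 | 0 | 0.10 |
| 1.00 | 0 | 0.00 |
| 1.00 | 0.20 | −0.20 |

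All values of f and u are assumptions. With identical knowledge of allocation throughout, kappa runs from 1.0 to below zero, depending only on how patients read the question.

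**Step 3: the reverse direction.** Because kappa = a − b, a value clearly away from zero would still show that answers differed by arm. The value that cannot be interpreted is one near zero, which is the value a reader would take as reassuring.

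**Step 4: pooling over arms.** Yes rates of 95% and 60% give 0.95 − 0.60 = 0.35; rates of 65% and 30% give 0.65 − 0.30 = 0.35. One kappa can stand for different patterns. That is a known limitation of the statistic, and publishing the arm-by-answer table resolves it.

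**The case against.** The best defence is that question 4 is evidently meant as the perception item announced in the Randomization and blinding section. Against a sham control, Yes for real treatment and No for not real is a plausible intended coding. The printed English may also be a loose translation of a clearer original, though that wording is not shown. It follows that a kappa can be computed mechanically, and a reader who infers that no usable answer is collected, or that kappa cannot be calculated, goes too far. What remains is that neither the coding nor the wording makes the result the agreement named in the analysis section. Condensation does not explain the gap either: the form is printed with its four items, and the text points to it for the details.

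Other inferences a reader might draw are not supported:

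- *This is the only evidence on blinding.* Question 1 scores sensation from 0 to 10 and can be compared by arm, and questions 2 and 3 record past experience. These bear on whether patients could tell the treatments apart, although none is a guess.
- *The trial will declare blinding intact.* The protocol says only that agreement will be quantified; it states no rule for success.
- *Kappa is the wrong statistic.* With a valid item, kappa does measure agreement between guess and allocation. An arm-specific index is a useful addition, not the correction of an error. Applying such an index to question 4 would need the same Yes/No coding that is in doubt here.

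**Conclusion.** The point holds in a limited form. Question 4 does not clearly elicit an allocation guess, its coding to EA or sham is not stated, and a kappa derived from it could be near zero even if patients knew their arm. Such a value would not be evidence that patient blinding held.

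The size cannot be fixed from the documents. Under complete unblinding and the assumed answers above, kappa falls anywhere between 1.0 and −0.20. How far it would be distorted in practice depends on how many sham patients say Yes because they were needled and how many EA patients say No because they are unsure.

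The consequence is confined to the blinding assessment and to confidence in the patient-reported secondary outcomes. It would be wrong to infer that the primary result is compromised: delirium is rated by blinded research registrars, and no planned efficacy analysis uses the questionnaire. The change should be made, and soon, because each patient answers the form only once and enrolment is planned to run from March 2025 to July 2026.

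**What to change.** - **Questionnaire.** For patients still to be enrolled, replace or supplement question 4 with: *Which treatment do you think you received? Electroacupuncture / sham electroacupuncture / don't know.*
- **Analysis.** Compute the agreement statistic from the new item and report the full arm-by-guess table, stating how *don't know* answers are handled. Preferably add an arm-specific index such as Bang's with a 95% CI, since it uses the *don't know* answers and shows each arm separately.
- **Patients who have already answered question 4.** Report the Yes rates by arm, separately. Do not label them as guesses or pool them with the new item.
- **If the form in use differs from Table 2.** Should it already contain an allocation guess, correct the printed table instead.

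The cost is one questionnaire item and a short change to the analysis text. The downside is that the guess will exist only for later enrollees, so the blinding assessment will rest on part of the 212 patients and two instruments will have to be reported side by side.
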